### Setting

The trial will be conducted in the urban site of Cap-Haitien and in the surrounding communities of Petite Anse, Fort Saint-Michel, and Madeleine, all located in Haiti’s Northern Department (Nord) (Fig. 3).

**Fig. 3 Fig3:**
[figure not shown]
Cap-Haitien and surrounding communities. Map by [name]

### Participant recruitment, eligibility, and screening

We will recruit eligible mother-infant dyads living in Cap-Haitien as well as the surrounding communities. To be eligible, mothers or caregivers must be individuals who are a minimum of 18 years old and are primary caregivers of an infant aged 6 to 8 months. Infants presenting evidence of a congenital health condition, severe disability, or severe malnourishment (weight-for-length Z-score < -3) will be excluded, because these factors may compromise child feeding and growth and can induce confounding in our results. Additionally, we will exclude children with allergies to ASFs (specifically eggs, milk, or fish) as well as those who are multi-birth infants (twin, triplet, etc.).

Prior to recruitment, potentially eligible mother-child dyads will be identified within Cap-Haitien and the three comparable communities of Petite Anse, Fort Saint-Michel, and Madeleine. The study team has conducted several studies in these communities and will draw on previously developed relationships and networks to recruit for this study in a timely manner. Community health agents, for example, regularly visit households throughout the communities and will assist in the identification and recruitment of eligible families. Additionally, medical records from the maternity and well-baby units at Fort Saint Michel clinic, and community rally posts will be used. The majority of mothers have access to cell phones, and numbers are contained in the medical records. Any information drawn from health records for mothers declining to be in the study will be destroyed.

Information sessions will be held in the communities to inform potential participants about the study. These strategies have previously enabled the team to canvas the entire catchment area and ensure all eligible mother-child pairs have equitable opportunity for entry into the study. Information sessions will be scheduled during off-work hours to better ensure all mothers have an opportunity to attend. If mothers express interest in participating, but are not able to attend the meeting, a separate enrollment date will be scheduled.

During the information sessions, the study coordinator will review and provide a full description of the study including information about the mothers’ obligations, surveys, and child nutrition and development measures. Once eligibility is established, study participants will go through the informed consent process individually. The study staff will provide the mothers with a verbal description of the study, which will explain the purpose of the study, their role in the study, and what to expect during data collection. The risks and benefits of the study will be explained to the study participants, and we will obtain written consent. Mothers will be permitted the necessary time (up until the child ages out of eligibility) to consider entry into the study to allow for careful decision-making.

Enrollment and one year of follow up are to be completed within a four-year timeframe for five respective cohorts. There will be five staggered enrollments, where 120 caregiver-infant dyads are recruited in each six-month cycle, with 40 participating dyads in each of the three study arms. All participants will be compensated for transportation costs and lost work or market time during enrollment and child assessments.

### Randomization

Using the website Randomization.com [65], we generated a list of randomization codes with a reproducible seed. These codes will be used to randomize the caregiver-infant pairs into one of the three study groups in a 1:1:1 ratio, with 200 dyads assigned to each study condition.

The randomization codes are set with 120 subjects randomized into eight blocks and with each block comprising 15 subjects. Within each block, each study arm is assigned five study subjects (Fig. 4). These 120 randomization codes will be used for each of the five enrollment cycles.

**Fig. 4 Fig4:**
[figure not shown]
Randomization Scheme

Prior to the start of each enrollment cycle, a staff member, who will not be directly involved with study participants, will print 120 paper slips marked with the generated random assignment codes, seal them in opaque envelopes, and bundle them in eight blocks of 15. Each block or bundle of 15 sealed envelopes will include a random sequence of five slips each for the three study groups. Each slip will be marked with the block and card number. These numbers will be recorded in a randomization log to enable data quality checks of the group assignments.

During enrollment, the study team will explain to the mother that her child will be randomly assigned to one of the three study groups. The team will subsequently remind the mother of the differences across the three groups, invite her to pick one envelope from a basket of multiple envelopes, and explain to her that the slip inside the envelope represents the group she and her child will be assigned to.

### Description of study conditions

#### Standard well-baby care

Children in all three groups will receive standard care, which is defined by the Essential Package of Health Services from Haiti’s Ministry of Public Health and Population (MSPP) [66, 67]. This package is provided by the Haitian government at community health centers and clinics and includes a World Health Organization immunization schedule of vaccines, high-dose vitamin A supplements, and growth monitoring and promotion.

#### Egg intervention

Mother-infant dyads randomized to the two intervention groups—nutrition intervention and multicomponent *Grandi Byen* intervention—will receive a weekly ration of seven eggs for the participating index infant and additional eggs for the household. Eggs for the nutrition intervention are sourced locally from a producer who supplied eggs for the pilot study. To ensure compliance and fidelity to daily egg feeding, caregivers in these treatment groups will be given a daily log specifically designed for them to record egg consumption as well as any incidences of diarrhea during the week. When caregivers receive their weekly ration of eggs, study enumerators will collect the data recorded on these logs as part of efforts to monitor compliance. Asking caregivers to record the child’s daily egg consumption encourages self-monitoring, which is known to encourage target health behaviors [68] and may consequently promote adherence to feeding the child with an egg daily. Moreover, social marketing messages targeting mothers in the intervention groups will emphasize the importance of giving one egg per day to the index child, while addressing strategies for getting the child to consume the whole egg. Mothers will also learn about practices for hygienic handling of eggs as well as preparation techniques to optimize child nutrition.

#### Parenting intervention

Mothers randomized into the multicomponent *Grandi Byen* arm will simultaneously participate in the egg intervention and a psychoeducational parenting intervention conveying messages on nutrition, WASH practices, and responsive parenting. Originally developed and tested in Uganda [39], the group-based intervention was adapted and piloted in Cap-Haitien by the study team. The intervention is rooted in social learning theory and employs active and interactive learning strategies such as verbal instruction, modeling (vicarious experience), direct experience, and receiving feedback [69]. It is also based on cognitive, behavioral, and interpersonal therapeutic techniques that encourage shaping of knowledge, problem solving, practicing new behaviors and eliciting family social support [70, 71]. Messages are delivered and reinforced through a facilitated peer-group platform. The parenting intervention has 12 modules, emphasizing several key messages that emerged in our pilot work and are known to support healthy growth and development: maternal self-care, child development (stimulating play, interactive communication, and healthy families), complementary feeding with ASFs and continued breastfeeding, and household hygiene practices such as handwashing and use of soap. An adapted program manual guides each session. Table 2 details the 12 intervention modules for the *Grandi Byen* parenting program.

**Table 2 Tab2:** *Grandi Byen* parenting intervention modules

No	Title	Session summary/empirical support	Targeted mechanism
1	Parenting for strong, healthy children	Parental aspirations; challenges encountered; introduces mothers to five principles of healthy parenting covered in *Grandi Byen*: *hygiene, food, play, conversation, self-care*. **All 5 are reinforced in every session.**	Responsive parenting
2	Strong, healthy families 1	Common family stressors that can impact child development and ways to address them. Need for positive home environment to help young children to thrive; strategies to build positive mother-infant interactions.	Responsive parenting
3	Taking care of yourself	Mothers are taught to identify and link their emotions and behaviors. Positive strategies to deal with negative emotions are introduced.	
4	Creating a stimulating environment for healthy development	Why young children need to play with objects in order to grow and learn; age-appropriate, readily available stimulating toys; mother-infant engagement	Responsive parenting
5	Talking and playing with children	New ways of talking to babies and why necessary; practice interacting with their child both verbally and non-verbally.	Responsive parenting
6	Animal source foods and diverse diets	What to feed and how much to feed infants/young children; continued breastfeeding; importance of diverse diets for young children, and why ASFs are critical in complementary feeding.	Nutrition^a^
7	Don’t forget the soap	Use of latrines and soap. Identifying barriers to handwashing and latrine use and how to overcome them.	WASH^a^
8	Positive family relationships	Strategies for positive communication and problem-solving skills for interpersonal conflict.	
9	Make play more challenging	Discusses why children need novelty and challenges. Identifies ways to make play more challenging. Identifies barriers to collecting new play things and strategies to overcome them.	Responsive parenting
10	Engaging with your children	Story-telling and other engaging activities (singing and dancing) are modeled by the facilitator and then practiced by mothers with their infants.	Responsive parenting
11	Strong, healthy families 2	This session builds upon earlier sessions focused on communication and family relationships and discusses ways to engage children’s father in play with their children. Mothers identify their own communication style and identity pros and cons of their style.	
12	Review session		

^a^Although only the primary focus of one session each, the importance of ASF and hygiene and sanitation will be reinforced weekly

Groups of 20 mother-child dyads will be formed based on location of residence in communities and will convene weekly in designated community sites (churches, schools, and community centers). Each session will last approximately one to two hours.

### Study measures

To evaluate intervention impacts, we will assess primary outcomes of child growth along with language, cognitive, motor, and social-emotional development milestones. Secondary outcomes of interest, which are also hypothesized to serve as mediating factors between the intervention and primary outcomes, include indicators for child health and nutrition (bone maturation, brain growth, respiratory or diarrheal infections, dietary intake, nutrient biomarkers), and responsive parenting based on observations of the home environment and parent-child interactions. Table 3 summarizes measures that correspond with outcomes of interest.

**Table 3 Tab3:** *Grandi Byen* study outcomes

Construct	Methods	Indicator	Timepoints
**Primary outcomes**			
Child growth	Anthropometric measures of height and weight	Length-for-age Z score (LAZ) Weight-for-age Z score (WAZ) Weight-for-length Z score (WLZ)	Baseline, 3 mo, 6 mo, 9mo, 12 mo
Cognitive, Language, Motor and Social Emotional Development	Ages and Stages Questionnaires (ASQ)– Social-Emotional, Communication, Gross Motor, Fine Motor, and Problem-Solving Domains	ASQ scores	Baseline, 6 mo, 12 mo
**Secondary outcomes**			
Responsive parenting	Parenting Interactions with Children: Checklist of Observations Linked to Outcomes (PICCOLO); Home Observation Measurement of the Environment (HOME), mother-infant observation	PICCOLO: Scores in Responsiveness, Affection, and Encouragement HOME: environment subscale will be used to measure aspects of the household environment (i.e., availability of toys/items for child to play with) and responsive parenting.	Baseline, 6 mo, 12 mo
Child dietary intake	24-hour recall and food frequency questionnaire	Nutrient intakes, dietary diversity, and ASF consumption	Baseline, 6 mo, 12 mo (24-hour recall) Baseline, 3 mo, 6 mo, 9 mo, 12 mo (food frequency questionnaire)
Child nutrient biomarkers	Blood draw, mass spectrometry (LC-MS-MS, CP-OES)	Plasma concentrations of nutrient biomarkers	Baseline, 6 mo
Child bone maturation	Ultrasound imaging of hand and wrist	Bone age Z score	Baseline, 6 mo, 12 mo
Child brain growth	Ultrasound imaging of the head until anterior fontanelle closes	Dimensions of brain regions (gangliothalamic ovoid, biparietal diameter, corpus callosum, other standard measures)	Baseline, 6 mo
Child morbidities	Blood draw, immulite immunoassay methods Stool samples 2-week morbidity recall by mothers	Plasma concentrations of inflammatory biomarkers (ovomucoid and ovalbumin IgE, C-reactive Protein [CRP], and Insulin-like growth factor 1 [IGF-1]). Diarrhea, respiratory conditions, allergies	Baseline, 6 mo
Child genetics	Buccal swabs	Targeted genomic analyses	Baseline

#### Primary outcomes

*Child growth* will be evaluated using anthropometric measures. Child weight and length will be measured following the WHO’s guidelines on child growth assessments [72]. Measurements will be obtained at five time points—baseline and at 3-, 6-, 9-, and 12-month follow-ups—using the Seca Model 874 (Digital) 440 lbs x 0.1-lb. resolution and the ShorrBoard® stadiometer, respectively. All measures will be repeated at least once to ensure precision. Weight and height measures that differ by more than 0.1kg and 0.7 cm, respectively, during the second measurement will be repeated a third time. Measures will be converted to weight-for-age (WAZ), weight-for-height (WHZ), and length-for-age (LAZ) Z-scores using WHO Growth Standards [73]. Ages will be calculated using the child’s date of birth reported at baseline.

*Child development* will be assessed using the Ages & Stages Questionnaires (ASQ) at baseline and at 6- and 12-month follow-ups. The ASQ, which has been used widely for developmental screening and studies in low- and middle-income countries [74], is a parent report measure of several aspects of child development including self-regulation, affect, and social communication in very young children. The Ages & Stages Questionnaires, Third Edition (ASQ-3) will be used to assess developmental milestones along the domains of *communication* (language), *problem solving* (cognition), *fine motor*, and *gross motor* development [75], while the Ages & Stages Questionnaires: Social-Emotional, Second Edition (ASQ:SE-2) will be used to examine changes in child *social-emotional* development [76].

#### Secondary outcomes

*Responsive Parenting* will be assessed using the Parenting Interactions with Children: Checklist of Observations Linked to Outcomes (PICCOLO) [77] and the infant-toddler Home Observation Measurement of the Environment (HOME) [78]. These assessments will be completed at three time points—at baseline and at 6- and 12-month follow-ups. The validated PICCOLO assessments measure nurturing parenting behaviors, present across diverse cultures worldwide, which determine psychosocial development during a child’s early years and throughout their life course [77]. For this study, we will specifically assess parenting behaviors along the PICCOLO domains of *responsiveness*, *affection*, and *encouragement.* The environment subscale from the HOME assessment will be used in addition to the three PICCOLO domains to measure aspects of the household environment in relation to child stimulation. Assessments with these instruments will be based on a combination of mother self-report and observations by study enumerators to assess interactions between the mother and child, and the quality and quantity of stimulation in the home environment [78, 79].

Because observation within the home environment is essential to assessing these constructs, study enumerators will complete the observation items on the HOME during visits to the participants’ homes. For PICCOLO assessments, mothers will be instructed to engage with their children as they typically would for 15 minutes, and their interactions will be videotaped. Independent raters, blind to the dyad’s study condition, will review and code five-minute segments per video, randomly selected from three five-minute segments. Raters will undergo extensive training and procedures will be put in place to ensure interrater reliability.

*Child dietary intake* and levels of different *nutrient biomarkers* will be evaluated as secondary nutrition outcomes. All caregivers will undergo a 24-hour dietary recall using the standardized multi-pass interview approach [22, 80] at baseline and at 6- and 12-month follow-ups. In the first pass, caregivers will be asked to list everything the child ate and drank in the last 24 hours. In the second pass, they will report the time of consumption, ingredients, and brands of each item listed in pass one. In the third pass they will be asked to give the closest estimated amounts the child consumed using measuring cups and graduated cylinders. Culturally appropriate visual aids such as cups, dishes, and pictures of foods are also provided in order to obtain the most accurate food measurements. Lastly, the items reported are all reviewed with the mother to ensure that the history is complete. Additional information, such as current breastfeeding status will also be obtained. The goal of the 24-hour recall interview is to capture the child’s usual daily dietary intake in order to correctly estimate nutrient intakes. Mothers will therefore be asked whether the dietary intake reported represents the child’s daily usual intake. A small subset of participants will undergo repeat 24-hour recalls to assess for intra-individual variability [22]. Records from the 24-hour recall will be entered into the *NutriSurvey* software (EBISpro, Germany) [81] which will analyze and estimate nutrient intakes for each infant. Data from the 24-hour recall interviews will also enable us assess child dietary diversity as well as changes in the consumption of Animal Source Foods (ASFs). Food frequency questionnaires will also be administered at baseline and at 3-, 6-, 9- and 12-month follow-ups.

To delineate the effect of the egg intervention relative to the multicomponent intervention, we will assess different biological indicators including levels of blood biomarkers of nutritional status at baseline and 6 months post-enrollment. We will examine changes in plasma concentrations of a suite of minerals—iron, zinc, iodine, and selenium. Plasma concentrations of vitamins (choline and vitamin B12), choline-related markers (methionine and betaine), and DHA will also be assessed. A trained phlebotomist will collect 3-4 ml of venous blood from the children using trace element-free sample collection methods and processing. Blood specimens will be aliquoted and processed using sterile methods to prevent environmental contamination and subsequently stored in a -80°C freezer. Plasma mineral concentrations will be measured using inductively coupled plasma mass spectrometry (ICP-MS; PerkinElmer NexION 2000) and inductively coupled plasma optical emission spectrometry (ICP-OES: PerkinElmer Optima 7300DV). For DHA and choline-related markers, liquid chromatography-tandem mass spectrometry (LC-MS/MS) will be applied to quantify them. Vitamin B12 levels, as well markers of inflammation, will be measured using Immulite immunoassay and other methods.

Inflammatory biomarkers will be assessed in relation to caregiver reports on *child morbidities* surveys during biweekly home visits*.* Specific biomarkers of interest are ovomucoid and ovalbumin immunoglobulin E (IgE) to evaluate risk of egg allergies, C-reactive Protein (CRP) as a marker of systemic inflammation, and Insulin-like growth factor 1 (IGF-1) as an indicator of growth.

A standard two-week recall on a range of infectious illnesses will supplement CRP data. Additionally, questions to assess diarrheal severity will include the frequency of diarrhea in the children, number of sick contacts within the household, presence of blood or fever, use of anti-microbials, and requirement for additional medical care at a clinic or local provider. A similar assessment for respiratory infections including cough, rhinorrhea, fever, rash, and lethargy will be obtained through the same two-week recall survey.

Stool samples and fecal swabs will also be essential for assessments on diarrheal and infectious outcomes, future assessment of microbiome changes, and relative biomarker changes. Samples collected at baseline and at 6- and 12-month follow-ups will be associated with assessments of current or recent (past 3 days) diarrheal disease. Our pilot data coupled with national data suggests a diarrheal prevalence of 30%, supporting adequate sampling at these intervals to estimate pathogen burden (unpublished observations—[name], Washington University School of Medicine). Stool samples will be collected from children using fecal swabs and fresh stool samples will be obtained, if available, from the child’s diaper. Should an unanticipated increase in diarrheal incidence be noted in the intervention arms, intensified efforts to identify pathogens associated with eggs (*Campylobacter* and *Salmonella*) will be pursued to determine if the egg preparations are increasing the risk of infectious diarrhea.

Ultrasound methods will be used to assess *bone maturation* at baseline and at 6- and 12-month follow-ups. *Brain growth* will also be assessed at baseline and 6 months post-enrollment using ultrasound*.* For bone maturation, ultrasound images of the child’s left hand and wrist will be obtained to assess maturity of the ossification centers. Following protocols used in our previous study in Ecuador [82], image findings will be adjusted for the child’s age and sex and indicated by the bone age Z-score (BAZ) using standards of Greulich and Pyle [83]. Additionally, brain ultrasound images will be obtained through the anterior fontanelle at baseline and 6 months. Images will assess the size of the gangliothalamic ovoid, corpus callosum, as well as ventricular diameter and extra axial space. Closure of the fontanelle will be noted, and in such cases, brain images will not be obtained. Our group conducted a feasibility study in Ecuador using a similar method [84], which will be implemented in the present study. Assessing intervention effects on child brain growth using these methods may support evidence related to DHA and choline’s role in brain development. All images will be obtained using the Mindray M7 Premium portable ultrasound with the 7L4s Linear Array Probe (Mindray North America, Mahwah, NJ).

The last biological indicator that will be evaluated is *child genetics* using buccal samples that will be obtained at the first study visit only. Buccal swab collection requires wiping the inside of the cheek with a nylon swab and placing the swab into stabilization solution. This minimally invasive and standardized technique allows for collection and preservation of genetic material and kept at room temperature for extended periods of time. Of note, interactions between host genetics, enteric pathogens, gut microbiota, and cognitive development are recently being recognized as an important component of child development [85–87]. The interpretation of the study results will almost certainly be impacted by the foresight to collect samples for retrospective targeted genomic analysis in association with the study findings.

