	Hypothesis 4: Children of mothers/caregivers receiving *Grandi Byen* will have higher scores on child cognition, language, motor, and socio-emotional development, with an effect size of 0.36 on cognition, compared to standard care and egg nutrition groups.

The first aim allows us to replicate findings from the *Lulun Project* in a new context of Haiti and extend them to determine the effect of an egg-only intervention on developmental outcomes. Eggs alone, however, do not target the other mechanisms through which poverty impacts child growth and development. The premise of this trial is that a “bundled” intervention that combines nutrition (eggs) with a parenting intervention highlighting responsive care, ASF consumption, and improved WASH practices will act in concert to synergistically improve child growth and development over and above that of an egg intervention alone. As well as targeting additional mechanisms (e.g., responsive parenting and cognitive stimulation to promote early learning), we theorize that mothers who receive reinforcement about the importance of ASF throughout the parenting intervention will be more adherent to providing the target child with one egg per day and will continue to provide their child with diverse diets incorporating affordable ASFs post-intervention, thereby sustaining expected growth and nutrition outcomes long after the intervention ends. Aim 2 will test for the additive and synergistic effects of an egg-only nutrition intervention (arm 2) and the multicomponent intervention (arm 3) compared to standard care (arm 1).

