Disentangling which specific elements (psychosocial or hygiene and sanitation practices) of the intervention did most to enhance the nutrition intervention may be useful for future adaptations to other contexts. However, our emphasis will be on the effects of the bundled intervention, which is a common practice in medical research [58, 59]. In aim 3, we will explore hypothesized pathways from the interventions to growth and development impacts (Fig. 2). The *Grandi Byen* intervention is anticipated to influence parenting practices through improvements in caregiving and child stimulation, household environmental conditions for WASH, and child feeding for dietary diversity and ASF consumption, which may in turn reduce infectious disease incidence, improve bone maturation, and increase blood concentrations of critical nutrients. By contrast, the egg intervention alone may affect nutrition biomarkers, infection, or bone maturation to a lesser extent but is unlikely to strongly influence child development outcomes. Finally, children in the standard well-baby care group should show little or no impacts on growth and development.

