The primary analytic model to test primary hypotheses of the primary study aims—aims 1 and 2 (Table 1)—is the growth curve analysis using hierarchical linear modeling (HLM) or hierarchical generalized linear modeling (HGLM), depending on whether the outcome variable is a normally distributed continuous variable or a categorical variable. In the current study, the different timepoints (i.e., five waves of data collection at baseline and 3-, 6-, 9-, and 12-month follow-ups) are nested within children. These clustering effects violate the independent-observation assumption embedded in a linear model, so we will use HLM (also known as a random-effect or mixed-effect model) to control for the nesting structure of the data. In this study sample, there is only one child per parent, thus the nesting effect of children within families is absent. We therefore plan to treat mother-child pairs as one study level. However, we apply a two-level HLM model that treats time as level 1 and children as level 2.

Aim 3 examines the pathways to child growth and development by testing a series of mediational effects of secondary outcomes: responsive parenting, child dietary diversity and nutrient intakes, biomarker status, allergies, bone maturation, acute diarrhea, and respiratory morbidity. To conduct HLM or HGLM analysis for this aim, we will employ the multilevel analysis specially developed for testing mediational effects [89]. The analysis will involve three models: a full model, a reduced model, and a model using the mediator as a dependent variable. For the time-to-event outcomes (diarrhea episode, respiratory infections, and allergies in first 6 months of follow-up), we will use a proportional hazards model [90, 91].

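### While eggs are supplied, all-foods dietary diversity and ASF scores rise in both egg arms because of the ration itself, so the contrast with standard care cannot be read as changed feeding practice

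*Protocol article*

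**What the plan says.** In the Protocol article, Secondary outcomes (child dietary intake), "caregivers will be asked to list everything the child ate and drank in the last 24 hours". The same recall, taken at baseline, 6 and 12 months, is to "enable us assess child dietary diversity as well as changes in the consumption of Animal Source Foods". Table 3 gives the indicators as "Nutrient intakes, dietary diversity, and ASF consumption", and the text adds: "Food frequency questionnaires will also be administered at baseline and at 3-, 6-, 9- and 12-month follow-ups".

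Under Egg intervention, arms 2 and 3 both receive seven eggs a week for the study child plus some for the family. Overview of study design sets the period at six months. The eligibility section counts eggs among ASFs. Caregivers in arms 2 and 3 keep a daily egg log, which is described as a compliance and self-monitoring tool.

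On interpretation, Study aims and hypothesized pathways says the Grandi Byen arm should improve parenting practices, including "household environmental conditions for WASH, and child feeding for dietary diversity and ASF consumption". It also predicts that mothers in that arm "will continue to provide their child with diverse diets incorporating affordable ASFs post-intervention". Statistical analyses lists the Aim 3 mediators, among them "responsive parenting, child dietary diversity and nutrient intakes, biomarker status".

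**The concern.** The construct in the pathway section is what caregivers choose to feed. The measurement described is everything eaten, including a food that the trial hands out. A child in arm 2 or 3 who eats the delivered egg counts as an ASF consumer and, if eggs form their own food group, gains one point of diversity, even if nothing else in the diet has changed.

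In the Aim 3 models, the mediator is then partly the treatment. During supply, the path from arm to diversity against standard care is positive for both egg arms by construction, and the plan tests one-sided in that direction. An apparent route through improved child feeding could be reported for an arm whose caregivers were taught nothing about diverse diets. A true change in feeding in arm 3 would be hard to tell apart from the ration when arm 3 is compared with standard care.

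**Working it through.** The plan states no figure for diversity or ASF consumption, so there is nothing to reproduce. The check has two parts.

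**1. Which measurements and contrasts are touched**

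| Measurement | Eggs supplied? | Arm 2 or 3 vs arm 1 | Arm 3 vs arm 2 |
|---|---|---|---|
| Baseline | No | Not affected | Not affected |
| 3 months (questionnaire only) | Yes | Raised by the ration | Only through differing adherence |
| 6 months (recall and questionnaire) | End of supply; the text does not say whether the recalled day is a supplied day | Raised if supplied | Only through differing adherence |
| 9 months (questionnaire), 12 months (both) | No | Level is off supply | Level is off supply |

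**2. Illustration of size**

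All inputs here are assumptions, except 200 per arm (Sample size) and one-sided testing (Statistical analyses). No other food changes, and eggs count as one food group.

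*Egg arm versus standard care.* Shift in mean score = c − p, where c is the share of egg-arm children eating an egg on the recalled day and p is the same share in control.
- Assume c = 0.5 to 0.9, p = 0.05 to 0.30 and a score SD of 1.0 to 1.5 groups.
- Smallest: 0.50 − 0.30 = 0.20 groups; 0.20/1.5 = 0.13 SD.
- Largest: 0.90 − 0.05 = 0.85 groups; 0.85/1.0 = 0.85 SD.

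A second set of assumptions lets a be the share eating the delivered egg, independently of eggs the family would give anyway. The shift is then [a + (1 − a)p] − p = a(1 − p).
- With a = 0.70 to 0.95 and p = 0.05 to 0.30, it runs from 0.70 × 0.70 = 0.49 to 0.95 × 0.95 = 0.90 groups.
- With an SD of 1.2 to 1.5, that is 0.49/1.5 = 0.33 to 0.90/1.2 = 0.75 SD.

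*Any-ASF consumption.* If 30 to 60% of control children eat any ASF (q), the egg-arm share is q + (1 − q)a.
- Over the same range of a, this runs from 0.30 + 0.70 × 0.70 = 0.79 to 0.60 + 0.40 × 0.95 = 0.98.
- The difference, (1 − q)a, runs from 0.40 × 0.70 = 28 points to 0.70 × 0.95 = about 67 points.

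*Chance that the ration alone gives a significant gain over control.* For a comparison at one visit with one-sided alpha 0.05 (assumed; the article states no level), probability = Φ(shift/(SD × √(2/200)) − 1.645).
- Smallest shift: Φ(0.20/0.15 − 1.645) = Φ(−0.31) = 0.38.
- c = 0.7, p = 0.30, SD 1.5: Φ(0.40/0.15 − 1.645) = Φ(1.02) = 0.85. This is the lowest value for any c of 0.7 or more.
- At the upper end it exceeds 0.99.

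*Arm 3 versus arm 2.* The shift is only the difference in egg adherence.
- Equal adherence: shift 0, and the error rate stays at 0.05.
- A gap of 5 to 20 points: 0.05 to 0.20 groups, or 0.05/1.5 = 0.03 to 0.20/1.0 = 0.20 SD.
- A 10-point gap: rejection probability from Φ(0.10/0.15 − 1.645) = 0.16 to Φ(0.10/0.10 − 1.645) = 0.26.

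With eggs left out of the score, the mechanical part is zero in every contrast.

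**The case against.** The strongest reply is that the article states no scoring rule: no food groups, no cut-offs and no ASF definition. Such rules often sit in an analysis plan, and this one is not shown. That stands as a limit. Counting the eggs is an inference from a recall of all foods with no exclusion. What remains is a mismatch within the article itself between the measurement described and the meaning given to it.

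It is also fair to say that egg intake is the exposure in both egg arms, so counting it is right for nutrient intake, total diet and the egg's own nutritional pathway. A mediator moved by treatment is what mediation requires. The difficulty arises only when the total is read as feeding practice. The pathway section does not claim that the egg-only arm will leave diversity or ASF consumption unchanged, so no contradiction on that point should be alleged.

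A reader might infer that the feeding-practice pathway cannot be read at all. The documents do not support that. Arms 2 and 3 get the same ration, so the contrast that isolates the parenting component largely cancels the shift. What is left is differing adherence. The protocol predicts this for arm 3, and it is caregiver behaviour, although it is egg feeding rather than diet diversification. The 9- and 12-month levels are off supply.

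A reader might also infer that a fall after month 6 will be taken as failure to sustain practice. No within-arm test of the 6-to-12-month change is specified, so this is a misreading to avoid rather than a planned error. Finally, the mediator list in Statistical analyses names diversity and nutrient intakes but not ASF consumption, so the any-ASF figures concern a secondary outcome and not a mediator listed there.

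**Conclusion.** The point holds in a limited form. During supply, differences from standard care in all-foods diversity and ASF consumption, and the Aim 3 path from arm to diversity against control, include the delivered egg and cannot be taken as changed practice. The possible shift is about 0.1 to 0.9 SD of the diversity score. This depends wholly on assumed adherence, control egg intake, score SD and eggs forming one food group, none of which is in the documents. Whether the 6-month recall is affected depends on whether the recalled day is still supplied.

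The primary outcomes are untouched. The consequence is confined to secondary diet indicators and the Aim 3 interpretation, but the remedy is cheap enough that it should be adopted.

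**What to change.** - From the same item-level data, derive diversity and ASF consumption twice: with all foods and without eggs. The recall already records ingredients. For the questionnaire, this assumes that eggs are a separate item.
- Use the all-foods version for total diet, nutrient intake and the egg-exposure pathway. Use the egg-free version as the feeding-practice mediator for measurements taken during supply.
- State whether the day recalled at 6 months counts as a supplied day.
- At 12 months, keep eggs in the score. They are no longer delivered, and continued egg feeding is part of the sustained ASF use that the protocol predicts. Test sustained practice by comparing arms at 12 months (arm 3 vs arm 2, and arm 3 vs arm 1), not by the 6-to-12-month change in all-foods ASF consumption, which mixes withdrawal of the ration with behaviour.

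The cost is one additional derived version of each indicator and a few lines of text, with no new data collection. The egg-free score during supply ignores eggs that a family buys itself, so the all-foods score should be reported beside it.
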